#### Secondary analyses

Mean changes in *Quick*DASH score, EQ-5D index, and grip strength over time (from baseline to 52 weeks) will be compared by using mixed model analysis of repeated measures and adjusting for respective baseline values. Mean treatment satisfaction and palmar pain scores at 12 and 52 weeks will be compared between the groups by using the *t* test. Mean total duration of sick leave from treatment start to 52 weeks will be calculated and compared by using Satterthwaite’s *t* test. Time to surgery (in days) will be analyzed by constructing Kaplan–Meier curves and comparing the groups with the log-rank test. Cost-effectiveness will be analyzed by using the incremental cost-effectiveness ratio. Three subgroup analyses will be carried out (in rank order): baseline CTS-6 score (≥3.0 versus <3.0), baseline nerve conduction results (severe/moderate versus mild/normal), and symptom duration (≥6 versus <6 months). Adverse events will be presented in tables. A *P* value of 0.05 will indicate statistical significance.

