### Follow-up procedures

Patients will complete a questionnaire consisting of disease-specific and generic patient-reported outcome measures at baseline and at 6, 12, 24, and 52 weeks after treatment start and will attend physical examination and nerve conduction testing at 52 weeks (Fig. 4). The trial coordinator (experienced research nurse) will monitor completeness of questionnaires and use telephone contact when necessary. Participants who choose to undergo surgery will be asked to complete the questionnaire shortly before surgery if the date of surgery precedes or is more than 2 weeks after the scheduled follow-up dates. Participants will be informed, in writing and during examination/follow-up, about the importance of completing the intervention and the follow-up procedures. Patients who choose to discontinue intervention are asked to, if possible, respond to the outcome questionnaires at the intervals defined in the protocol and attend the 1-year follow-up.

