#### Outcome measures

The CTS-6 is a validated questionnaire inquiring about severity, frequency, and duration of symptoms—including nocturnal and daytime pain and numbness or tingling—experienced by the patient in the past two weeks [17]. Each item has five possible response options, which range from 1 (no symptom) to 5 (most severe symptom). The symptom score is the mean of all answered items; higher scores (1 to 5) indicate worse symptoms. The *Quick*DASH is a short form of the disabilities of the arm, shoulder, and hand (DASH) questionnaire, a widely used outcome measure for upper extremity disorders, including CTS [18]. The *Quick*DASH consists of 11 items concerning difficulties in performing activities with five response options (from no difficulty to unable to perform an activity). Higher score (0 to 100) indicates worse activity limitations. The EuroQol 5-dimensions (EQ-5D) is a widely used measure of general health and quality of life; the EQ-5D-5 L version will be used [19]. The palmar pain scale is a two-item scale measuring pain in the palm and related activity limitations; higher score (0 to 100) indicates more pain and activity limitations [20]. Treatment satisfaction will be measured with a visual analog scale asking the patients to rate (on a scale of 0 to 100) their satisfaction with their current hand status with regard to symptoms and ability to use it in daily activities (higher score indicates higher satisfaction).

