### Sample size

In a previous study, patients with idiopathic CTS improved on average by 1.6 points in the CTS-6 score (range of 1 to 5) at 12 weeks after surgery [20]. No previous data regarding change in CTS-6 score after use of wrist splinting or soft bandage are available. A score improvement of 0.7 corresponds to improvement by one severity level in four of the six items (i.e., from severe to moderate, moderate to mild, or mild to no symptoms, in more than half of the items). If the soft bandage is assumed to have no effect, it would correspond to “no treatment”. A previous study found that the mean change in CTS-6 score in a group of patients who completed the CTS-6 on two occasions with 1–3 weeks’ interval *without treatment* was 0.03 (95% confidence interval (CI) of −0.07 to 0.12) [17]. With 90% power, 5% significance level, two-sided tests, and mean changes (baseline to 12 weeks) in the CTS-6 score of 0.7 in the splint group (standard deviation of 0.9) and 0.1 in the soft-bandage group, a sample of 48 patients per group will be needed. To account for possible dropouts, we plan to recruit 112 patients.

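### Satisfaction is declared as a change endpoint but tested on raw follow-up means without baseline, and palmar pain is tested at a visit where it is not an endpoint

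*Protocol article*

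**What the plan says.** Secondary endpoints in the protocol article names a change in the satisfaction score at 12 and 52 weeks. In the same list palmar pain is a plain score at 52 weeks, so the list separates change endpoints from raw ones.

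Secondary analyses then gives the test: "Mean treatment satisfaction and palmar pain scores at 12 and 52 weeks will be compared between the groups by using the" *t* test. The other secondary change endpoints that it covers are handled differently. One sentence covers QuickDASH, the EQ-5D index and grip strength, and its closing part reads: "grip strength over time (from baseline to 52 weeks) will be compared by using mixed model analysis of repeated measures and adjusting for respective baseline", meaning each measure's own starting score. Primary analyses treats the change in CTS-6 in the same way, with a mixed model adjusted for the baseline score.

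Two further places bear on whether a baseline satisfaction score exists. Outcome measures says that patients rate "their satisfaction with their current hand status with regard to symptoms and ability to use it in daily activities". Follow-up procedures says: "Patients will complete a questionnaire consisting of disease-specific and generic patient-reported outcome measures at baseline and at 6, 12, 24, and 52 weeks", counted from the start of treatment.

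**The concern.** The declared quantity and the tested quantity differ. A change endpoint needs a baseline value, and the planned test uses none. Two analysts working from this text could report different quantities for the same endpoint, one a difference in change and the other a difference in follow-up means. Blinding states that patients cannot be blinded, and satisfaction is a subjective rating, so this choice should be closed before anyone sees data.

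Precision is the second issue. If a baseline score is available, a test that ignores it has a wider confidence interval than the baseline-adjusted model used for the other change endpoints.

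The palmar pain part is simpler. A 12-week test is planned for which no endpoint is declared.

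**Working it through.** **1. The sections side by side.**

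| Outcome | Endpoint as declared | Planned analysis | Baseline used? |
|---|---|---|---|
| CTS-6 | change | mixed model | yes |
| QuickDASH | change | mixed model | yes |
| EQ-5D index | change | mixed model | yes |
| Grip strength | change | mixed model | yes |
| Satisfaction | change, 12 and 52 weeks | *t* test on means, 12 and 52 weeks | no |
| Palmar pain | score, 52 weeks | *t* test on means, 12 and 52 weeks | no (none implied) |

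Satisfaction is the one change endpoint whose analysis leaves out baseline. Palmar pain has one test more than its endpoint allows for.

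**2. The plan's own figure.** Sample size gives "With 90% power, 5% significance level, two-sided tests" and mean changes "in the CTS-6 score of 0.7 in the splint group (standard deviation of 0.9) and 0.1 in the soft-bandage group", and concludes that "a sample of 48 patients per group will be needed". Taking the SD of 0.9 as common to both arms, the difference is 0.7 − 0.1 = 0.6, and

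n per arm = 2 × (1.960 + 1.282)² × 0.9² / 0.6² ≈ 47.3, rounded up to 48.

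The figure reproduces. It concerns CTS-6 only and does not depend on how satisfaction is analysed. No power is stated for satisfaction.

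**3. Precision.** Let r be the correlation between baseline and follow-up satisfaction. The article does not give it, so a range is assumed, with equal SDs at the two times. Relative to the raw *t* test, the variance of the treatment effect is:

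- baseline-adjusted analysis: 1 − r²
- *t* test on change scores: 2(1 − r)

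The fourth column is 48 / (1 − r²). The fifth takes an effect that the raw test detects with 80% power.

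| Assumed r | Adjusted, 1 − r² | Change score, 2(1 − r) | Per arm for the raw test to match 48 adjusted | Power when adjusted |
|---|---|---|---|---|
| 0.2 | 0.96 | 1.60 | 50 | 81.6% |
| 0.3 | 0.91 | 1.40 | 53 | 83.6% |
| 0.5 | 0.75 | 1.00 | 64 | 89.9% |
| 0.7 | 0.51 | 0.60 | 94 | 97.5% |

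Leaving out baseline therefore gives up 4%, 9%, 25% or 49% of the variance. The third column shows that making the test match the label literally, with a *t* test on change scores, is worse than the raw means when r is below 0.5. Only adjustment improves on the raw test throughout. It also answers the change question, because with baseline as a covariate the group difference is the same whether the outcome is the follow-up score or the change.

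**4. Missing visits.** Missing values states that missing scores are not replaced. Each *t* test therefore omits patients without a score at that visit, whereas a mixed model would still use their other visits.

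**The case against.** The strongest objection is that no text names satisfaction as a baseline measure. The abstract's account of the baseline questionnaire names CTS-6, QuickDASH and EQ-5D. Follow-up procedures does not list the scales, and the schedule figure is not available here. The other change endpoints are worded as running from baseline to a visit; satisfaction is not. The word *change* in the endpoint list may be the slip, and the *t* test the intended analysis. This stands as a limit on the remedy. It does not remove the contradiction: if baseline is collected, the test ignores it, and if it is not, the declared endpoint cannot be computed.

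It can also be said that preferring adjustment is a choice of method, and that the planned test loses nothing against a change-score *t* test unless r exceeds 0.5. That is correct. The precision loss is relative to the model that the plan already uses for its other change endpoints. The unseen statistical analysis plan might settle the matter, but the article as written fixes two different things.

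A reader might draw stronger conclusions that the document does not support:

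- **Bias.** Allocation is randomized 1:1. Chance baseline imbalance is noise that the standard error already covers.
- **A definite gain of 10–33% in effective sample size.** That is 1/0.91 to 1/0.75 and holds only if r lies between 0.3 and 0.5, which is an assumption.
- **Every other repeated patient-reported score gets a mixed model.** Palmar pain is patient-reported and shares the *t* test. The accurate statement concerns change endpoints.
- **Patients who miss one visit are lost altogether.** Someone missing at 12 weeks still counts at 52 weeks.

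**Conclusion.** The point holds as an inconsistency with a modest efficiency cost. The endpoint list and the analysis section disagree on what is measured for satisfaction and on when palmar pain is tested. Both disagreements can be read directly from the text.

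The size of the precision loss depends on r and on baseline satisfaction being collected, and neither is stated. Collection is a fair inference from the word *change*, from the baseline questionnaire, and from an item about current hand status that can be answered before treatment. If r is about 0.3 or less, the loss is at most 9% of the variance.

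Statistical analysis reserves confirmatory testing for the primary endpoints. Satisfaction and palmar pain are secondary and non-confirmatory, so the primary conclusions and the 48 per group do not change.

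**What to change.** First establish from the schedule of assessments whether satisfaction is recorded at baseline.

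- **If it is:** keep the change endpoint and analyse satisfaction with the baseline-adjusted mixed model already planned for QuickDASH, with between-group contrasts at 12 and 52 weeks. Do not substitute a *t* test on change scores. No further covariate is needed for this purpose.
- **If it is not:** reword the endpoint as the satisfaction score at 12 and 52 weeks, and the planned *t* test then fits. Recruitment began in June 2018, so baseline scores for patients already enrolled could not be recovered.
- **Palmar pain:** test it at 52 weeks only, or add the 12-week score to the secondary endpoints.

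The cost in either case is a change of wording in the protocol or analysis plan, made before the data are analysed. No additional patients are needed, and no new data collection.

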### Randomization

Patients will be randomly assigned in accordance with a computer-generated randomization list (ratio of 1:1) [16]. The randomization will be stratified in accordance with patient sex and carried out in random blocks of various sizes (4, 6, and 8). An administrative assistant, not involved in the trial, will prepare sequentially numbered sealed opaque envelopes containing the group allocation. After providing written informed consent and undergoing the baseline assessment by a study investigator (orthopedic surgeon), the enrolled patient will proceed to the hand therapist, who will open the envelope with the lowest number and provide the patient with either a wrist splint with a metal bar or a soft bandage in accordance with treatment allocation (Fig. 1).

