## Discussion

CTS is a very common condition affecting millions of people around the world [27]. Despite weak evidence, wrist splinting, alone or in combination with a variety of treatments, is currently the most common non-surgical treatment around the world.

A few previous studies have evaluated wrist splinting in the treatment of CTS by using the 11-item symptom severity scale (Boston CTS questionnaire), a scale that corresponds to the CTS-6, to measure symptoms [17]. A previous study that came closest to a placebo-controlled design compared two types of splints: a conventional rigid wrist splint (*n* = 46) and a soft splint (*n* = 45) that limits motion of the metacarpophalangeal joints but does not immobilize the wrist (although it is unclear whether full flexion was possible) [28]. The mean symptom severity score at baseline was 2.9 in both groups, and despite a small to moderate improvement at 3 months, the results at 9 months showed only a small mean score change (0.4 and 0.3, respectively), a difference of uncertain clinical importance.

In a study comparing steroid injection with 1-month night-time wrist splinting [29], the baseline mean symptom severity score in the splint group (*n* = 25) improved by 0.38 (standard deviation of 0.5) at 8 months (from a relatively low mean baseline score of 2.0). In another study comparing platelet-rich plasma injection with 6-month night-time wrist splinting, the mean symptom severity scores in the splint group (*n* = 60) were 1.7 at baseline and 1.5 at 6 months [30]. In a randomized study that compared electroacupuncture with 4-month night-time wrist splinting [31], the mean symptom severity score in the splint group (*n* = 91) was 2.4 at baseline and had changed by only 0.09 at 4 months.

In a study comparing ultrasound-guided pulsed radiofrequency with 12-week night-time wrist splinting, the mean symptom severity score in the splint group (*n* = 18) improved from 3.0 at baseline to 2.0 at 12 weeks [32]. Thus, although the studies assessing wrist splinting alone have reported conflicting results, the majority have shown small changes in the symptom severity score even with splinting longer than the time used in clinical practice.

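### The ratio named as the only analysis of 52-week cost-effectiveness breaks down if the effect difference is small, which this design makes plausible; net monetary benefit avoids this

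*Protocol article*

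**What the plan says.** The Secondary endpoints section lists cost-effectiveness at 52 weeks as one of ten secondary endpoints. Secondary analyses gives the method in one sentence: "Cost-effectiveness will be analyzed by using the incremental cost-effectiveness ratio". No other method is named, and the article does not say whether effect means CTS-6 points, EQ-5D index, QALYs or operations avoided.

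The only effect the protocol quantifies for design is at 12 weeks. Sample size assumes "mean changes (baseline to 12 weeks) in the CTS-6 score of 0.7 in the splint group (standard deviation of 0.9"). The comparator arm is planned to change by 0.1, which makes the design difference 0.6. It concludes that "a sample of 48 patients per group will be needed" and adds: "To account for possible dropouts, we plan to recruit 112 patients". The same section reports a mean CTS-6 gain of 1.6 points at 12 weeks after surgery in an earlier study.

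Under Interventions, patients with little or no improvement are offered surgery in both arms, with no operation before week 12. In the Discussion, the cited study nearest to a placebo-controlled design compared a rigid with a soft splint; its 9-month results "showed only a small mean score change (0.4 and 0.3, respectively"). The Background says that long-term efficacy has not been established.

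**The concern.** A ratio of cost difference to effect difference has a usable interval only when the effect difference is clearly away from zero. When it is not, the 95% confidence set for the ratio is unbounded, and small changes in the data can turn a large positive ratio into a large negative one. A negative ratio alone is also ambiguous: a treatment that is cheaper and better gives the same number as one that is dearer and worse.

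Several features of this trial make a small 52-week difference plausible. Surgery is available in both arms for most of the year, and the protocol's own figure for the gain after surgery exceeds the planned gain from either device. The cited 9-month difference is 0.1 points. The trial's second hypothesis, fewer operations with the splint, would itself pull the symptom difference down, because more bandage patients would then have had the surgical gain.

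At stake is one secondary endpoint. The Background and Discussion use cost as part of the case for the trial. Choosing another method only after the ratio had proved uninterpretable would be a post hoc change.

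**Working it through.** **Reproducing the plan's figure.** Inputs from Sample size: difference 0.7 − 0.1 = 0.6, SD 0.9, and "With 90% power, 5% significance level, two-sided tests". Then n = 2 × (1.960 + 1.282)² × 0.9² / 0.6² = 47.3, so 48 per group, as stated. With 112 recruited and a "computer-generated randomization list (ratio of 1:1") there are 56 per arm; 48/56 = 0.857 leaves room for about 14% loss.

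**Method.** The Fieller 95% set for a ratio is a bounded interval only if the denominator differs from zero at the two-sided 5% level. Let d be the true effect difference and m = d / (SD × √(2/n)). Then:
- P(no bounded interval) = Φ(1.96 − m) − Φ(−1.96 − m)
- P(effect estimate has the wrong sign) = Φ(−m)

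**Inputs.** The protocol gives no 52-week difference, so d is a scenario. The value 0.1 is the cited 9-month difference (0.4 − 0.3); 0.6 is the 12-week design difference carried forward. SD 0.9 is the design value. SD 0.5 is the only SD of a long-term change in the Discussion (8 months, splint arm of a steroid-injection comparison).

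**Worked case.** With d = 0.1, SD 0.9 and n = 48, SE = 0.9 × √(2/48) = 0.184 and m = 0.54. P(no bounded interval) = Φ(1.42) − Φ(−2.50) = 0.915. P(wrong sign) = Φ(−0.54) = 0.293.

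| d | SD | n per arm | m | No bounded interval | Effect estimate of wrong sign |
|---|---|---|---|---|---|
| 0.1 | 0.9 | 48 | 0.54 | 0.915 | 0.293 |
| 0.1 | 0.9 | 56 | 0.59 | 0.910 | 0.278 |
| 0.1 | 0.5 | 48 | 0.98 | 0.835 | 0.164 |
| 0.1 | 0.5 | 56 | 1.06 | 0.815 | 0.145 |
| 0.3 | 0.9 | 48 | 1.63 | 0.628 | 0.051 |
| 0.6 | 0.9 | 48 | 3.27 | 0.096 | under 0.001 |

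A simulation of 200,000 draws at n = 48 and SD 0.9 agreed (d = 0.1: 0.916 and 0.293; d = 0.6: 0.095 and 0.0006). An unbounded interval is more likely than not when d is below 1.96 × SD × √(2/48): 0.36 for SD 0.9, 0.20 for SD 0.5.

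**Effect of surgery on the denominator.** Let p and q be the proportions operated on in the splint and bandage arms. Suppose operated patients gain 1.6, the others keep 0.7 or 0.1, and these changes last to week 52. Then

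d = [1.6p + 0.7(1 − p)] − [1.6q + 0.1(1 − q)] = 0.6 + 0.9p − 1.5q.

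This is zero when q = 0.4 + 0.6p, and below 0.36 when q exceeds 0.16 + 0.6p. The protocol states no surgery rates, so these are assumed (SD 0.9, n = 48):

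| Splint p | Bandage q | d | No bounded interval |
|---|---|---|---|
| 20% | 20% | 0.48 | 0.257 |
| 40% | 40% | 0.36 | 0.500 |
| 40% | 50% | 0.21 | 0.792 |
| 40% | 60% | 0.06 | 0.938 |
| 40% | 70% | −0.09 | 0.922 |

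The mixture is crude, since it ignores that those who go to surgery are the ones who improved least. It shows direction and rough size only.

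**EQ-5D denominator.** No difference or SD is stated. Assuming SD 0.15 to 0.25 and n = 48, P(no bounded interval) is 0.90 to 0.93 for a difference of 0.02, 0.63 to 0.84 for 0.05, and 0.10 to 0.50 for 0.10.

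**The case against.** A reader might infer that, on the protocol's own figures, the 52-week effect is expected to be near zero, so the ratio will usually have no finite interval and may carry the wrong sign. The documents do not support that. No 52-week effect is stated. The 0.1 comes from one cited study that used the 11-item scale, measured at 9 months and had a different comparator. Pairing it with the 12-week SD makes a scenario, not a plan figure. The only design effect, 0.6, would give a bounded interval about 90% of the time if it lasted. The Trial objective section treats durability to 12 months as the question under test, and the Discussion also cites a splint group that improved more at 6 months (0.73) than at 6 weeks (0.48), although that is a within-group change. The wrong-sign probability belongs to the effect estimate; the sign of the ratio also depends on the cost difference, for which there are no figures.

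Two further points have force. A QALY denominator would accumulate over the year, so early benefit would count even if the arms converged by week 52. And a journal article commonly leaves interval methods, the cost-effectiveness plane and acceptability curves to the full plan, so their absence is no fault.

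All of this stands and makes the point conditional and minor. It does not remove it, because the point concerns the method the article does name. Simply carrying 0.6 forward also ignores surgery from week 12. Net monetary benefit does not shrink the uncertainty in costs or effects, but it gives an interval that is always bounded and a sign with one meaning.

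**Conclusion.** The point holds in conditional form. As the only named analysis, the ratio is fragile if the 52-week effect difference is small or reversed. The surgery pathway, the cited 9-month result and the unestablished long-term efficacy make that plausible, but nothing in the protocol makes it the expected result.

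The size depends almost wholly on the unknown effect. A true difference of 0.1 CTS-6 points would leave the ratio without a bounded interval in roughly four of five trials or more; a sustained 0.6 would do so in about one in ten. These figures assume a CTS-6 denominator, normal estimates and SDs borrowed from other time points; the EQ-5D and surgery-rate scenarios rest on assumed inputs. The ambiguity of a negative ratio read alone needs no such assumption. This is a minor point on a secondary endpoint, and the confirmatory conclusions do not depend on it.

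**What to change.** In Secondary analyses, base cost-effectiveness inference on incremental net monetary benefit: λ × (difference in QALYs) − (difference in cost), over a stated range of threshold values λ, with bootstrap 95% intervals and an acceptability curve. Take QALYs over 52 weeks from the EQ-5D at baseline and at 6, 12, 24 and 52 weeks, adjusted for the baseline value. Report the cost and effect differences separately with intervals, and keep the ratio beside them as a descriptive summary.

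This changes analysis wording only: the EQ-5D and cost data are already to be collected. The downside is that a threshold range must be named in advance. If the full analysis plan already works this way, one sentence brings the article into line. The change should be fixed before unblinded data are seen.

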### Statistical analysis

For continuous endpoints (CTS-6, *Quick*DASH, patients satisfaction, palmar pain, EQ-5D index, grip strength, time to surgery, and sick leave duration), mean values and standard deviations will be calculated. For categorical variables (rate of surgery and adverse events), proportions will be calculated. Statistical tests will be performed in accordance with the intention-to-treat principle. An exploratory as-treated analysis will also be performed.

Both hypothesis-generating and confirmatory testing will be performed, the latter for the primary endpoints. Multiplicity issues will be addressed in compliance with the European Medicines Agency’s Guideline on multiplicity issues in clinical trials. More specifically, the primary endpoints are ranked according to clinical relevance, and confirmatory claims will not be based on an endpoint with a rank lower than the variable whose null hypothesis was the first that could not be rejected. The subgroup analyses will be carried out in rank order.

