#### Primary analyses

The change in CTS-6 score from baseline to 12 weeks (primary outcome) will be compared in the two groups by using mixed model analysis of repeated measures and adjusting for the baseline score. The rate of surgery at 52 weeks (co-primary outcome) will be compared by using Cox regression analysis with fixed follow-up time and the Huber–White estimator [25, 26] and adjusting for age, dominance of the study hand, and baseline CTS-6 score; relative risks with 95% CIs will be calculated. As supportive analysis the chi-squared test will also be performed.

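### Splitting baseline CTS-6 at 3.0 for the first-ranked subgroup analysis loses at least about 36% of the information on effect modification by severity, if the score is roughly normal and the modification linear

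*Protocol article*

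**What the plan says.** Under Secondary analyses, the protocol article lists three subgroup analyses in rank order, each with two classes: "baseline CTS-6 score (≥3.0 versus <3.0), baseline nerve conduction results (severe/moderate versus mild/normal), and symptom duration (≥6 versus <6 months". The Statistical analysis section adds: "The subgroup analyses will be carried out in rank order". It reserves confirmatory testing for the primary endpoints, so the subgroup analyses are hypothesis-generating.

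The scales behind the three variables differ:
- **CTS-6** is nearly continuous: "The symptom score is the mean of all answered items; higher scores (1 to 5) indicate worse symptoms".
- **Nerve conduction** is already a four-grade classification (Table 1).
- **Symptom duration** appears as an inclusion floor of 1 month and as the 6-month cut. The article does not say how finely it is recorded.

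Under Primary analyses, the 12-week comparison uses "mixed model analysis of repeated measures and adjusting for the baseline score", with no cut stated for that score.

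The trial is sized for the main effect: "With 90% power, 5% significance level, two-sided tests", with mean changes of "0.7 in the splint group (standard deviation of 0.9" and "0.1 in the soft-bandage group", so that "a sample of 48 patients per group will be needed".

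**The concern.** The first-ranked subgroup question is whether baseline symptom severity changes the benefit of the splint. The score can take many values between 1 and 5, yet the stated analysis uses only which side of 3.0 a patient falls on. Scores of 2.9 and 3.1 are treated as different, while 3.0 and 4.8 are treated as alike. If the effect changes gradually with severity, the position of each patient within a class is thrown away.

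A trial sized for its main effect has limited power for effect modification to begin with, and the split lowers it further. At stake is a greater chance of reporting no sign that severity matters when there is one. No confirmatory claim depends on it.

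**Working it through.** **1. The plan's own figure.** Inputs from Sample size: difference 0.7 − 0.1 = 0.6, SD 0.9 (taken as common to both groups), two-sided 5%, power 90%.

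n per group = 2 × (1.960 + 1.282)² × 0.9² / 0.6² = 2 × 10.51 × 2.25 = 47.3, rounded up to 48. This matches. The recruitment target of 112 against 96 analysed implies 1 − 96/112 = 14.3% dropout. The article gives no figure for interaction power.

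**2. Information kept by a two-class split.** For a linear treatment-by-modifier interaction under 1:1 allocation, the split keeps a share equal to the squared correlation between the modifier and its two-class version. For a normal modifier cut at c SDs from its mean, with share p above the cut, this is φ(c)² / [p(1 − p)].

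**3. Baseline CTS-6 cut at 3.0.** The article gives no baseline distribution for this trial, so these are assumptions.
- 3.0 is the median: 0.3989² / 0.25 = 0.637 kept, 36.3% lost. This is the minimum for a normal score.
- Mean 2.9, SD 0.7: c = 0.1/0.7 = 0.14, p = 0.44, 36.8% lost.
- Means 2.6 to 3.4, SDs 0.6 to 0.8: 36% to 46% lost.
- Other shapes: a uniform modifier cut at its median loses 25%. A true step at the cut loses nothing.

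**4. Symptom duration cut at 6 months.** Assumed lognormal and truncated at 1 month, with median 4 to 24 months and log-SD 0.8 to 1.2: 33% to 80% lost on the log scale. This applies only if duration is recorded as a time.

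**5. Nerve conduction, four grades to two.** Grades scored 0 to 3.
- Equal shares: variance of the score 1.25, variance of the split 0.25, covariance 1.25 − 0.75 = 0.50. Kept: 0.50² / (1.25 × 0.25) = 0.80, so 20% lost.
- Shares 10/40/40/10: covariance 1.10 − 0.75 = 0.35. Kept: 0.35² / (0.65 × 0.25) = 0.754, so 25% lost.
- Over 11 grade mixes: 9% to 29% lost. Of 20,000 random mixes, 8% reached one third.

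**6. Power, closed form.** Normal modifier cut at its median, SD 0.9, N = 96, difference in effect between halves 0.6 (as large as the whole design effect).
- Split: SE = 0.9 × √(16/96) = 0.367; 0.6/0.367 − 1.96 = −0.33; power 37%.
- Continuous: slope = 0.6 / (2 × √(2/π)) = 0.376 per SD; SE = 0.9 × √(4/96) = 0.184; 0.376/0.184 − 1.96 = 0.09; power 54%.
- With N = 112: 42% versus 60%.

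**7. Power, simulated.** 6,000 replicates per cell, main effect 0.6, residual SD 0.9, N = 96, cut at the mean, both tests adjusted for the continuous modifier. Type I error was 4.9% to 5.5% over the settings run.

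| Change in effect per SD | Split | Continuous |
|---|---|---|
| 0.2 | 13% | 18% |
| 0.3 | 24% | 34% |
| 0.4 | 38% | 55% |
| 0.5 | 53% | 74% |

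The article states no interaction size, so the rows are a range.

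**The case against.** The strongest reply is that prespecified, ranked, exploratory subgroups with fixed cuts are a defensible choice. The article names the subgroups but not the model, so the full protocol or SAP may already specify a continuous interaction. Where interactions are modest the gain is small: at 0.2 per SD both tests have little power. The larger gains need strong modification. At 0.5 per SD around an average of 0.6, the effect would be 0.1 at one SD below the mean and 1.1 at one SD above. A continuous term also assumes linearity. All of this stands and keeps the point minor. It does not make the split the better basis for inference on a near-continuous score.

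A reader might infer more than the document supports:
- **That all three splits lose a third or more.** Nerve conduction typically loses 20–25%, and its split falls where Table 1's motor latency changes from normal to abnormal. The figure for duration depends on how it is recorded.
- **That a miss on the first subgroup undermines the next two.** The stopping rule is written for the primary endpoints. For the subgroups the article states an order and no gate.
- **That adjusting for the score and then splitting it is a contradiction.** The two uses serve different purposes. The adjustment only shows that the uncut score is available to the model.
- **That 3.0 is an arbitrary value.** No reason is given, but it is the midpoint of the 1-to-5 scale, and a condensed article may omit the reason.

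**Conclusion.** The point holds as a minor improvement. For baseline CTS-6, the stated split loses at least about 36% of the interaction information, given a roughly normal score and roughly linear modification. At N = 96 that costs about 5 points of power at 0.2 per SD and about 17 points at 0.4 per SD. For symptom duration the loss is about 33% or more on the log scale, conditional on its being recorded as a time. For nerve conduction grade it is typically about 20–25%, with a recognisable boundary behind the split. Every percentage rests on assumed distributions. The primary analyses, the sample size and the confirmatory claims are untouched.

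**What to change.** Base the first subgroup inference on a treatment-by-continuous baseline CTS-6 interaction in the existing mixed model. Do the same for log symptom duration if it is recorded as a time. Optionally add a four-level trend for nerve conduction grade. Keep the rank order, and report the stated two-class estimates as a descriptive display. If an unpublished analysis plan already does this, no change is needed.

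The cost is a wording change and one interaction term per variable, with no extra patients or visits. The CTS-6 score and the nerve conduction grade are already collected. The downside is an assumed linear trend, which the two-class display helps readers check.
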